#### Message development

The above messages originated from a multiple-stage development. First, a literature review was performed to identify published knowledge, attitude, and behavior barriers to rational use of antibiotics among RTI patients and measures used to tackle these barriers. Second, tentative lists of the barriers and corresponding messages helpful in overcoming the barriers were generated based on the literature review and results from our previous research findings. Third, two rounds of consensus meetings were organized to select, refine, and form a preliminary message package from the lists of barriers and counter messages. Fourth, “think-aloud” interviews with the presenting RTI patients and their doctors at 6 selected township and community health centers were carried out to test the comprehensibility and acceptability of the preliminary message package. Fifth, a final 12-item message package was derived based on these “think-aloud” interviews.

#### Message tailoring

The study uses a novel computerized method in tailoring the messages to the need and context of individual patients. More specifically, each of the messages is designed as a template inserted with substitution variables to be replaced with relevant values and/or text according to the actual conditions and contexts of the patient under concern. Taking the example of the message to be sent on day 1 (Table 1), it contains seven variables specified as “[PatientName],” “DiseaseDiagnosis,” etc. When sent to a patient, for example, named “Li Si,” who has consulted doctor Zhang San at “SanXiaoKou Community Health Center” for sneezing, stuffy nose, and sore throat and the doctor diagnosed the illness as “common cold.” The message is changed to: “Dear Li Si, many thanks for your trust and visit to our clinic for a common cold. What you were experiencing were mainly sneezing, stuffy nose and sore throat. These are very common symptoms. They generally reach a peak within 1-3 days and then begin to relieve gradually. You needn’t see any doctor again unless you do not get better within 14 days. From [name] with SanXiaoKou Community Health Centre.”

Most of the substitution variables are determined by built-in computerized algorithms based on literature reviews or findings from the research team’s previous investigations and the expert consensus mentioned earlier. Taking the example of the “normal duration,” the online system has a built-in “dictionary” which reads like {“diagnose 1”: duration 1, “diagnose 2”: duration 2, …, “diagnose *n*”: duration *n*}. So, the online system can automatically provide a relevant duration value upon the diagnose entered by the doctor.

#### Message sending

The whole process of the message selection, modification (substitution of embedded variables), and sending will be by a user-friendly mini computer program. The program automatically extracts data about the patient’s name, symptoms, and diagnosis from the electronic medical record system routinely in use at all the participating clinics and then translates all the substitution variables into personalized texts. So, implementation of the intervention incurs little additional workload for the participating doctors. What the doctors need to do is limited to obtaining informed consent and cell phone numbers from the patients and adding them into the list eligible to receive the TMP; Fig. 2 illustrates how the mini program works. The upper part of the figure provides a name list of all the messages to be sent out to patients. The middle part shows an example message template and the doctor is allowed to modify the template for his/her own patients, while the lower part presents all the substitution variables capable of being automatically translated.

**Fig. 2 Fig2:**
[figure not shown]
Screen print of the mini computer program for designing and tailoring intervention messages

#### Intervention adherence

Pragmatic measures will be used to improve intervention adherence from both doctor and patient perspectives. For doctors, adherence will be enhanced by (1) one session training of doctors in the intervention arm on TMP content and benefits; (2) user-friendly online system which minimizes the doctors’ workload in using the TMP; (3) automatic recording and presentation, via the online system, of individual doctor’s intervention performance (e.g., absolute number and percent of RTI patients who have been sent the TMP) as compared with his/her peers; and (4) award of continued education credits for doctors who meet a preset performance standard (e.g., delivery of TMP to 80% of the RTI patients encounters during the study period). Similarly, measures for improving patient compliance will include the use of tailored and easily comprehensible TMP, delivery of highly relevant messages during a “time-window” when the patients are seeking professional help, and prior advice by the doctors during the initial consultation on the need to read the TMP in the forthcoming days.

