### Allocation to study arms

The recruited township or community health centers will be randomly allocated to TMP and UC arms at the same time after the completion of baseline data collection. The allocation process will be performed by an external statistician via 4 steps. Step 1, the project facilitator sends, via email, the allocation requirements alongside the name-list of the 6 selected counties and the 4 health centers recruited under each of the counties to the external statistician. Step 2, the statistician performs the random assignment of the health centers into equal arms of TMP and UC using the “random sample of cases” function in IBM SPSS on a county-by-county base so that the 4 health centers recruited from each of the site counties is randomly assigned as 2 to the TMP arm and the other 2 to the UC arm. Step 3, the statistician emails back the resultant allocation to the project facilitator. Step 4, the facilitator communicates the allocation to the participating physicians and arranges the planned training for those in the TMP arm.

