### Interventions

#### Usual care

The intervention will be tested against usual care. In other words, the control group will maintain usual care, while the intervention group patients will receive, in addition to usual care, 12 short messages in 12 consecutive days after the consultation. Here, usual care refers to the existing procedures (mainly, history inquiries, physical checkup, lab tests, clinical diagnosis, and prescribing treatment) being routinely practiced in the consultation and management of patients with RTIs. Using UC as the control condition is advantageous in at least a couple of senses: it involves almost no further changes in the control group and is thus most easy to implement the trial; it allows to assess the added value of the TMP upon the existing care and should thus meet with the least barriers in disseminating the trial results.

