#### Data collection

The study data will be collected through one baseline and five follow-up telephone interviews. For any recruited patient, the baseline interview happens immediately after the consultation, while the follow-up interviews are scheduled at 7, 14, 21,180, and 365 days after the baseline. The interviews will be performed by trained data collectors using a structured questionnaire adapted from our previous study [18] (Additional files 1, 2, 3 and 4). The main content of the questionnaire includes patient demographic characteristics (e.g., sex, age, education, residential area, and medical insurance status), illness duration, symptoms, severity rating, diagnosis, antibiotics, and other medicines prescribed. EPI DATA 3.1 will be used to create a data entry interface for all the on-site and telephone follow-up interviews. Table 3 summarizes measure by measure time schedule for data collection.

**Table 3 Tab3:** SPIRIT schedule of outcome measures

**Category**	**Outcome measure**	**Initial consultation**	**Days after consultation**				
			**7**	**14**	**21**	**180**	**365**
Primary measure	Number of days with antibiotics use	√	√	√	√		
Secondary measures	Illness duration	√	√	√	√		
	Illness severity	√	√	√	√		
	Times of re-visits				√		
	Antibiotics re-prescription				√		
	Knowledge about and attitude toward antibiotics					√	√
	Times of re-occurrence of RTIs					√	√
	Health service seeking for re-occurred infections					√	√
	Antibiotics consumption for re-occurred infections					√	√
	Quality of life (EQ-5D-5L)	√	√	√	√		
	Attitude toward intervention messages		√	√			
	Understanding of intervention messages		√	√			

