## Discussion

Both physicians and patients play important roles in antibiotic prescribing and uptake, while contemporary efforts in China have been focused primarily on doctors, with far less attention being put on patients. This study will determine the efficacy of a 12-message intervention to educate patients to reduce excessive antibiotic use. The intervention is innovative in a number of ways. First, the messages are designed to tackle existing problems identified through scoping literature reviews and field investigations [28–32]. Second, the messages are sent to patients at a unique time when they are suffering from RTIs and thus are at increased need for help in coping with their illness. Third, the messages are closely linked to the patients’ symptoms and diagnosis and are easily been felt as relevant and acceptable. Fourth, the intervention is facilitated by a computerized program and its implementation incurs little additional work load on the physicians. If proved effective, the intervention should be acceptable to both patients and physicians and scalable to other areas.

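### Doctors in the TMP arm alone get training, delivery feedback and credits, so an effect on antibiotic days cannot be credited to the patient messages alone, and index prescribing is not an outcome

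*Protocol article*

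**What the plan says.** **The contrast and the conclusion.** The Usual care section defines the difference between the arms as 12 messages sent after the consultation. It defends a usual-care control because "it allows to assess the added value of the TMP upon the existing care" and because "it involves almost no further changes in the control group". The Discussion states: "This study will determine the efficacy of a 12-message intervention to educate patients to reduce excessive antibiotic use". The Conclusion section is worded similarly.

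**What TMP-arm doctors receive.** The Intervention adherence section lists "one session training of doctors in the intervention arm on TMP content and benefits", an online display of each doctor's "absolute number and percent of RTI patients who have been sent the TMP" set against that of peers, and "award of continued education credits for doctors who meet a preset performance standard", with delivery to 80% of RTI encounters as the example. Doctors also advise patients, in the initial consultation, to read the messages. The Allocation section confirms that training follows allocation and is for one arm only: "the facilitator communicates the allocation to the participating physicians and arranges the planned training for those in the TMP arm". The Blinding section says that doctors are unblinded and that the TMP comes up in the encounter.

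**The outcomes.** In Table 2 the primary outcome is every day with any antibiotic, from onset to day 21 after the consultation. The prescribing outcomes are re-prescription in the same episode and prescriptions for recurrent episodes. Prescribing at the index consultation is not listed, although the Data collection section says that the questionnaire covers "illness duration, symptoms, severity rating, diagnosis, antibiotics, and other medicines prescribed".

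**The concern.** The arms differ in what happens to the doctors as well as in what is sent to the patients. The subject of the training is the package itself, whose Day 3 and Day 8 texts in Table 1 say that antibiotics are mostly unnecessary for these illnesses. Every message carries the doctor's name. A doctor trained on this material, who then introduces it to the patient, may write fewer antibiotic prescriptions before any message goes out.

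Fewer index prescriptions and lower uptake of prescribed antibiotics both appear as fewer antibiotic days. The Background justifies the trial by saying that past efforts concentrated on doctors and that patients were neglected. If part of the effect ran through doctors, a conclusion about educating patients by message would go beyond the evidence, and so would a decision to scale up the messages without the doctor components.

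**Working it through.** **1. The plan's own figures.** Inputs from the Sample size section: control mean 4.35 days, SD 2.06, target 20% of 4.35 = 0.87 days, alpha 0.05 (two-sided reproduces the figure), power 90%.

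- Per arm: 2 × (2.06 × (1.960 + 1.282) / 0.87)² = 117.8, rounded up to 118, as stated.
- Total: 2.45 × 118 × 2 × 1.2 × 1.2 = 832.6, rounded up to 833, as stated.

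The sample size is not in dispute here. It only supplies the 0.87-day yardstick.

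**2. Arms side by side.**

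| Component | TMP arm | Usual care arm | In the stated contrast? |
|---|---|---|---|
| 12 messages to patients | yes | no | yes |
| Training of doctors on the package | yes | no | no |
| Peer comparison of delivery | yes | cannot apply | no |
| Credits for delivery | yes | cannot apply | no |
| Doctor's advice to read the messages | yes | cannot apply | no |

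**3. How large a doctor effect could be.** The documents give neither of the following, so both are assumptions:

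- r = relative fall in index antibiotic prescribing in the TMP arm
- s = share of control-arm antibiotic days that come from the index prescription. It can be below 1, because the outcome also counts days before the consultation and antibiotics obtained later.

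With no message effect and unchanged days per antibiotic user, the difference in days is 4.35 × s × r.

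| s | Difference at r = 10% | Share of 0.87 | r needed for 0.87 days: 0.87 / (4.35 × s) |
|---|---|---|---|
| 1.0 | 0.435 days | 50% | 20% |
| 0.8 | 0.348 days | 40% | 25% |
| 0.6 | 0.261 days | 30% | 33% |

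If index prescribing stood at 80% (the Background gives over 80% for antibiotic use in general, so this too is an assumption), falls of 20%, 25% and 33% would bring it to 64%, 60% and 53%.

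**4. Timing.** The Allocation section places randomization after baseline data collection is complete. The Data collection section places each patient's baseline interview right after the consultation. Read literally together, every index consultation would precede allocation and training, and index prescribing could not be affected. But the Patient recruitment section sends investigators to centers already in intervention and control arms, and the Blinding and Intervention adherence sections have the TMP raised during the consultation. These statements cannot all hold.

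**The case against.** - **Delivery staff must be trained.** An intervention sent through clinics needs trained clinic staff, the protocol describes the training openly, and TMP as delivered versus usual care is a legitimate pragmatic contrast. This stands. A reader might infer that the randomized comparison is confounded or invalid; the documents do not support that. Only the attribution is in question.
- **The incentives do not target prescribing.** Feedback and credits reward sending messages, and the advice is only to read them. The Message sending section describes the doctor's task as little more than consent, phone number and listing the patient. This stands too. A reader might infer that doctors are taught or rewarded to prescribe less; the text says only that training covers the content and benefits of the package. An effect on prescribing is an inference from Table 1, plausible but not a stated aim.
- **Index prescribing is recorded and could be reported under an SAP that is not shown.** In part. How to analyze it can be left to an SAP. But this article itself sets out the outcome list, the description of the contrast and the wording of the conclusion, and those do not match the intervention that it describes.
- **Allocation follows baseline, so index prescribing is safe.** This reading conflicts with three other sections, as shown above. It is a reason to reconcile the text rather than to dismiss the point.

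**Conclusion.** The point holds as a limit on attribution. The trial can estimate the effect of the TMP as delivered, including training, feedback and advice. As written, it cannot show that the messages alone produced that effect.

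Under the assumed inputs, a 10% relative fall in index prescribing would account for about 0.26 to 0.44 days, or 30% to 50% of the target. A reader might go further and say that a doctor effect could explain the entire 0.87 days. That needs a 20% relative fall even if every antibiotic day comes from the index prescription, and 33% if 60% do. Nothing in the documents suggests that one training session achieves this, so it is an upper case.

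The mechanism also requires that index consultations follow allocation and training, which most but not all of the text implies. This is an improvement worth making, not a flaw that invalidates the trial.

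**What to change.** 1. Add antibiotic prescribing at the index consultation (yes/no, and days prescribed if recorded) to Tables 2 and 3 as a pre-specified secondary or process outcome. Report it by arm with a confidence interval that accounts for clustering. Messages start after the consultation, so an arm difference could not come from that episode's messages.
2. State the objective and conclusion as the effect of the TMP as delivered, naming the doctor training, feedback and advice.
3. Set limits on interpretation in advance:
   - Do not adjust the primary analysis for index prescribing, since allocation may affect it.
   - Do not take a non-significant difference across 24 centers as proof that the messages alone worked.
   - Note that an arm difference could also arise from unblinded recruitment after the consultation, not only from doctors' behavior.
4. Reconcile the Allocation section with the Blinding, Intervention adherence, Patient recruitment and Data collection sections on whether index consultations come before or after allocation and training.

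The cost is wording and one extra table row from data already collected. The downside is a more modest claim about the messages alone.

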### Trial evaluation

#### Outcome measures

The primary outcome is the number of days of antibiotics use, including antibiotics obtained before and after the initial consultation. The secondary outcomes include (1). illness duration and severity, (2) patients’ attitude and understanding of intervention messages, (3) patients’ quality of life, (4) re-visits and antibiotic usage, (5) patients’ knowledge and attitude toward antibiotics, and (6) recurrence of RTIs and related health service and antibiotics use. Definition and calculation of these measures are summarized in Table 2.

**Table 2 Tab2:** Primary and secondary measures for trial evaluation

Measure	Definition/calculation
**Primary measure**	
-Number of days with antibiotics use	Days of antibiotics use from onset of the RTI to the initial consultation + days of antibiotics use from day 1 to 21 after the initial consultation based on the patient’s responses to question item A5d in Additional file 1, B2 in Additional file 2, and item C2-C4 in Additional file 3. Here, days of antibiotics use is defined as days on which the patient has used any antibiotics.

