#### Sample size

The sample size of patients to be recruited for the trial evaluation is calculated on the basis of the primary outcome measure above. Our previous study [18] estimated that the number of days of antibiotic use by symptomatic RTI patients was 4.35 $$\pm$$ 2.06 for rural township health centers in Anhui province. There is no internationally agreed minimally important difference in the days of patients using antibiotic. However, we anticipate that a reduction of at least 15% in the days of antibiotic use would represent a meaningful change at the population level. So, we assume the following: (1) the intervention group is 20% lower than the control group, i.e., a reduction of about 0.87 days; (2) standard deviation of the days of antibiotics use is 2.06 days; and (3) the alpha value is 0.05. Given these, to detect a possible absolute difference of 0.87 days in the rates with 90% power, we will need 118 RTI patients in each arm. Based on our previous study results the estimated design effect value would be 2.45. By allowing for a 20% attrition rate and for a 20% loss to follow-up rate, therefore we would aim to recruit at least 2.45×118×2×1.2×1.2=833 patients into the study and this translates into about 35(833/24=35) patients per township/community health center.

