#### Patient recruitment

In order to evaluate the trial, 35 patients diagnosed with RTIs from each of the site township or community health centers will be recruited using a consecutive strategy. More specifically, each of the health centers in the intervention and control arms will be sent one investigator and from the start date when he/she arrives at the site, all incoming patients with RTIs will be invited to participate after consultation until a preset number of eligible patients have been recruited. The field investigator will conduct the recruitment face-to-face after obtaining informed consent from participants.

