#### Data analysis

The data collected will be used to compare the differences between the control and intervention groups as a whole and between subgroups in the intervention arm in terms of days of antibiotic use per episode of RTIs; times of re-visits to clinics and antibiotics re-prescription for the same RTI; quality of life; times of re-occurrence of RTIs and related health service seeking and antibiotics consumption for re-occurred infections; and scores of patients’ knowledge about and attitude toward antibiotics.

Estimation of statistical significance and confidence intervals will assume a type I error established in alpha=0.05, using the IBM SPSS V25 statistics package. Missing data will be treated as missing at random and imputed using a chained-equations multiple imputation model. Initial data analysis will consist of descriptive summaries intended to examine the patterns of the various measurements and check for normality of the continuous variables. And necessary transformations will be explored and selected, if necessary, to induce approximate normality. Regarding the numerical variables between two groups, *t*-test of independent samples for mean comparisons will be carried out. The chi-square test will be conducted for categorical variables (non-continuous). Lastly, no interim analysis is planned.

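### The primary outcome counts antibiotic days taken before any message is sent, and the stated unadjusted test passes any arm difference in those days straight into the result

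*Protocol article*

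**What the plan says.** **Outcome.** The Outcome measures section states: "The primary outcome is the number of days of antibiotics use, including antibiotics obtained before and after the initial consultation". Table 2 makes this a sum, "Days of antibiotics use from onset of the RTI to the initial consultation + days of antibiotics use from day 1 to 21" after that consultation. The parts come from item A5d (Additional file 1), item B2 (Additional file 2) and items C2 to C4 (Additional file 3).

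**Timing.** Under Usual care, intervention patients receive "12 short messages in 12 consecutive days after the consultation". Under Patient recruitment, "all incoming patients with RTIs will be invited to participate after consultation".

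**Analysis.** For numerical variables the Data analysis section names a t-test: "test of independent samples for mean comparisons will be carried out". It names no baseline covariate, and it allows transformations towards normality.

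**Sample size.** A previous study "estimated that the number of days of antibiotic use by symptomatic RTI patients was 4.35", with an SD of 2.06. The plan assumes "the intervention group is 20% lower than the control group, i.e., a reduction of about 0.87 days" and "standard deviation of the days of antibiotics use is 2.06 days". It does not say whether these figures include days before the consultation.

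**The concern.** Antibiotic days between symptom onset and the consultation are a baseline characteristic. Here they are added to the endpoint instead of being used to adjust it. Three consequences need checking:

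- An arm difference in prior use is counted as if it were an effect of the messages.
- The sum may be more variable than the part the messages can influence.
- If the 4.35 days include prior use, a 20% fall in the days that can still change is less than 0.87 days on the total.

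Prior use is unlikely to be negligible. The Background says patients in rural areas can easily obtain antibiotics from pharmacies without a prescription. The eligibility criteria exclude only those who already sought treatment for this illness at a participating centre.

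**Working it through.** **1. The plan's own figure.** Inputs from the Sample size section: difference 0.87 days, SD 2.06, alpha 0.05 (two-sided reproduces the figure), power 90%.

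n per arm = 2 × [2.06 × (1.960 + 1.2815) / 0.87]² = 117.8, so 118. Then 118 × 2 × 2.45 × 1.2 × 1.2 = 832.6, stated as 833. Both reproduce. So 118 per arm is the effective number after the design effect and losses, and it is used below.

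**2. Pass-through.** Total = pre + post, so the arm difference in the total equals the difference in pre plus the difference in post. The messages can change only the second. Without differential recruitment the first has expectation zero but is not zero in any one trial.

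**3. Size of a chance imbalance.** SE = SD_pre × √(2/118), taking the same design effect for pre-consultation days. SD_pre is not in the documents, so the values are assumed.

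| SD_pre (assumed) | SE | 95% range | Share of 0.87 |
|---|---|---|---|
| 0.5 | 0.065 | ±0.13 | 15% |
| 1.0 | 0.130 | ±0.26 | 29% |
| 1.5 | 0.195 | ±0.38 | 44% |

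**4. Variance of the sum.** Var(total) = SD_pre² + SD_post² + 2ρ × SD_pre × SD_post, where ρ is the pre/post correlation. If 2.06 describes post-consultation days only and ρ = 0, SD_pre of 0.5, 1.0 or 1.5 gives a total SD of 2.12, 2.29 or 2.55. Power for 0.87 days at 118 per arm is then 88%, 83% or 75%. The added variance disappears at ρ = −SD_pre / (2 × 2.06), that is −0.12, −0.24 or −0.36. At more negative correlations the sum is the less variable measure.

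**5. What adjustment does.** With A5d as a covariate in an untransformed linear model, total = pre + post implies that the slope on A5d differs by exactly 1 between the two outcomes. The arm coefficient is the same. The patient-level residual SD is SD_post × √(1 − ρ²) for either outcome. With SD_pre 1.0 and SD_post 2.06:

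| ρ | SD of total | SD of post | Residual SD, adjusted |
|---|---|---|---|
| 0.25 | 2.50 | 2.06 | 1.99 |
| 0 | 2.29 | 2.06 | 2.06 |
| −0.25 | 2.05 | 2.06 | 1.99 |
| −0.5 | 1.78 | 2.06 | 1.78 |

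In none of these cases does adjustment give a larger SD than either unadjusted outcome.

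**6. The assumed effect.** If the 4.35 days include a pre-consultation mean m (assumed) and the messages cut later days by 20%, the effect on the total is 0.20 × (4.35 − m). Power is at 118 per arm with SD 2.06. The last column is 0.87 / (4.35 − m).

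| m | Effect on total | Power | Cut in later days needed for 0.87 |
|---|---|---|---|
| 0 | 0.87 | 90.0% | 20% |
| 0.5 | 0.77 | 81.9% | 23% |
| 1.0 | 0.67 | 70.5% | 26% |
| 1.5 | 0.57 | 56.6% | 31% |

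Steps 4 and 6 rest on opposite readings of 4.35 ± 2.06 (later days only, or the whole episode). Their losses are alternatives and must not be added.

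**The case against.** **The whole episode is a coherent quantity.** The Data analysis section speaks of days per RTI episode, so counting from onset may be deliberate. Adding a component the messages cannot reach leaves the expected absolute arm difference unchanged. This stands: the definition is not an error of logic, and a whole-episode total can still be reported. It does not justify comparing that total without adjustment.

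**Covariates may be left to an analysis plan that is not shown.** This stands in part. The outcome definition and the test are both stated here, and together they produce the problem. A reader might extend the point to baseline adjustment of severity and EQ-5D-5L. That is the kind of detail an analysis plan commonly supplies, and it is not part of this point.

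**Imbalance is not bias.** Centres are allocated at random, two and two within each county, and recruitment is consecutive. Chance imbalance therefore averages zero and belongs to the sampling error. A reader might infer that the primary estimate is biased. The documents do not show that. Doctors and site investigators are unblinded (Blinding section), so differential recruitment is possible, but it is not established. If it occurred, it would also affect later antibiotic use, and changing the outcome window would not cure it. If centres are allocated only after patient baselines are complete, as the allocation section can be read, such selection is less likely.

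**Extra noise is not certain.** Patients already treated may take fewer days later. Step 4 shows that a sufficiently negative correlation cancels the added variance, so a definite loss of power cannot be claimed.

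**Conclusion.** The point holds as a weakness in how the stated outcome and the stated test fit together. Pre-consultation days cannot respond to the messages, and the unadjusted t-test carries any arm difference in them fully into the primary result.

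The size can only be given as a range. For an assumed pre-consultation SD of 0.5 to 1.5 days and the plan's 118 effective patients per arm, chance imbalance has a 95% range of about ±0.13 to ±0.38 days. The sum is more variable than later days alone unless the two parts are sufficiently negatively correlated. If 4.35 days is a whole-episode figure, a 20% cut in later days gives less than 0.87 days on the total, for example 0.67 with a pre-consultation mean of 1 day.

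A reader might also infer that the sample-size arithmetic is wrong. It is not: 118 and 833 reproduce. What is unstated is the window to which the mean, the SD and the 20% apply.

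**What to change.** **Minimum change.** Keep all items as collected. Analyse the primary outcome in a linear model that accounts for clustering by centre, with pre-consultation antibiotic days (A5d) as a covariate. This does not redefine the outcome and needs no new data.

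**Preferred change.** Define the primary outcome as antibiotic days 1 to 21 after the consultation, keep A5d as the covariate, and report the whole-episode total as secondary. In an untransformed linear model the arm coefficient is the same under either definition, so the gain is a headline result confined to days the messages can affect. The equality fails if the outcome is transformed, which the Data analysis section permits, so the plan should fix the scale in advance.

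**Also needed.** State the window to which 4.35 ± 2.06 refers, and give the mean, SD and target reduction for the window chosen. Neither redefinition nor adjustment removes the smaller absolute effect in step 6; only a restated assumption deals with that.

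**Cost.** Recruitment opened on 1/12/2022. Redefining the primary outcome therefore needs sponsor permission, ethics approval and a report to the registry, as the section on protocol amendments sets out. Adding the covariate alone avoids redefining the outcome.
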